**Fig. 2 Fig2:**
[figure not shown]
Contents and points of data capture: Standard Protocol Items: Recommendations for Interventional Trials (SPIRIT) schedule of enrolment, interventions, and assessments. ELISA, enzyme-linked immunosorbent assay; NIV, non-invasive ventilation; CT, computed tomography; APACHE, acute physiology and chronic health evaluation

### Safety and adverse events monitoring

In this trial, safety will be monitored by an independent data safety and monitoring board (DSMB) team comprising clinical physicians, evidence-based medicine experts, and statisticians. The safety assessment with respect to the vital signs, routine blood and urine tests, hepatic and renal function, fecal occult blood test, and electrocardiogram results will be conducted at every visit to avoid adverse events (AEs).

The DMSB assigns the severity of AEs as mild, moderate, severe, or serious adverse events (SAEs). Any AEs that occur during the study process should be recorded in the AEs form, including the time, severity, and duration of the AEs, the measures adopted, and the outcomes. These AEs will be addressed appropriately, and the treatment measures and results will be recorded. The subjects with AEs will be followed up. The mild AEs and SAEs are followed up until the adverse reactions disappear and the laboratory indicators return to the normal or the baseline level.

The relationships of AEs to the research medication are assessed as “impossible”, “suspicious”, “possible”, “probable”, or “definite” by the DMSB. The causal judgment indicators include whether the administration time and the suspected AEs exhibit a reasonable relationship; whether the suspected AEs fulfill the criteria for the typical reactions of the drug; whether the AEs can be explained by the effects of the combined drug, patient’s clinical condition, or other therapies; whether the suspected adverse reactions disappear or are mitigated after discontinuation of the drug; and fwhether the same reaction recurred after repetitive administration of the research medication.

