### Withdrawal or dropout criteria

Patients will not be included in the analysis if:The researchers find out after randomization that the participants were included by error or misdiagnosis.Participants were not administered the research medication as planned because:They received the research medication for > 24 h;They failed to receive the research medication;They received the research medication for < 5 days (not including the patients who were discharged due to improved health or death due to progression of the illness);The actual dosage was < 80% of the total dosage (compliance < 80%).The major data were missing, affecting the evaluation of the efficiency of the main indicators.Prohibited medication was used or the combined medication dosage exceeded that of the protocol, thereby affecting the evaluation of the efficiency.Due to complications or changes in the condition, other specific treatment measures were accepted that were not suitable for continuation in this study.Voluntary withdrawal.

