### Statistical analysis

An independent professional statistician and researcher will develop a complete statistical analysis plan for the trial, prior to the final analysis. The statistical analysis will be performed by the statistician in a blinded manner using the Statistical Analysis System (SAS) software version 9.2. The main analysis will be based on the full analysis set (FAS). According to the intention-to-treat principle, the FAS refers to a set of data on any participants who randomly receive at least one treatment. The per-protocol set (PPS), a subset of the FAS, includes data on only those participants who completed the trial without any violations of or deviations from the protocol. The FAS and PPS will be used for the assessment of efficacy. For the safety assessment, the safety set (SS) will be used, which includes patients who have received at least one safety evaluation after treatment.

All data, including the number of subjects included, drop-outs, elimination conditions, demographics, baseline characteristics, and efficacy and safety assessment, will be analyzed using different approaches. Descriptive and univariate statistics will be used to characterize the study participants and compare the baseline characteristics between the two groups. The primary outcome is the rate of endotracheal intubation, which will be determined by the Cochran-Mantel-Haenszel (CMH) test in the FAS population. We prefer to use the CMH chi-square test because it can deal with confounders of multi-center effects. Two-sided tests will be performed for all the other statistical analyses. The CMH chi-squared test or Fisher’s exact test will be used for comparing the categorical outcomes. The continuous outcomes will be analyzed by Student’s *t* test, while the AEs will be presented using descriptive statistics and compared using a chi-square test. A *P* value <0.05 will be considered to indicate statistical significance. Missing data will be explored and adjusted using the imputation method.

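### Seriousness is used as a fourth grade of adverse event severity, and the safety set is defined by a post-treatment evaluation instead of by exposure: a minor correction to two definitions

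*Protocol article*

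**What the plan says.** Two sections of the protocol article bear on this.

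**Safety and adverse events monitoring.** The monitoring board "assigns the severity of AEs as mild, moderate, severe, or serious adverse events (SAEs". On recording, the rule is broad: "Any AEs that occur during the study process should be recorded in the AEs form". The items named for that form are given as "including the time, severity, and duration of the AEs, the measures adopted, and the outcomes". Severity is among them, and no separate item for seriousness is named. On follow-up, the section first says that subjects with adverse events will be followed up, without limiting this to any grade. The next sentence is narrower: "The mild AEs and SAEs are followed up until the adverse reactions disappear" and laboratory values return to normal or baseline.

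**Statistical analysis.** For safety, "the safety set (SS) will be used, which includes patients who have received at least one safety evaluation after treatment". For efficacy, "the FAS refers to a set of data on any participants who randomly receive at least one treatment". The planned treatment of safety data is brief: "the AEs will be presented using descriptive statistics and compared using a chi-square test".

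**The concern.** Severity describes how intense an event is. Seriousness describes its consequence, such as death or a prolonged hospital stay. An event can be of moderate intensity and serious, or severe and not serious. Making them levels of one variable forces a choice between two facts that should both be kept.

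The safety set raises a different question. A safety population is normally fixed by exposure. Here, membership depends on something that happens after exposure, namely being evaluated. A patient with a very early bad outcome is the one least likely to meet that condition. The article's Objectives section puts safety in the first primary objective, so both definitions should be clean.

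**Working it through.** The article states no adverse event figure that could be reproduced, so the check compares the definitions with one another.

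**1. The severity scale**

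- Intensity has three levels (mild, moderate, severe) and seriousness has two (yes, no), which gives 3 × 2 = 6 possible combinations.
- The article's scale has 4 codes. Read as mutually exclusive, three of them hold the non-serious events, one for each intensity. The fourth holds all serious events.
- The three serious combinations therefore collapse into one code. An event coded as an SAE has no intensity grade, and the severe code holds only severe non-serious events.
- The total number of adverse events and the number of SAEs are unaffected. What is lost is the intensity of the serious events and a complete count of severe events.
- Nothing among the named form items recovers the lost attribute. That list is introduced as what the form includes, so it need not be complete.

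**2. The safety set against the FAS**

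- FAS: randomised and at least one treatment received.
- Safety set: at least one safety evaluation after treatment.
- A patient who receives one infusion and then dies or withdraws with no evaluation afterwards meets the first condition and fails the second.

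How many patients this could affect depends on what after treatment means.

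- *After the first dose.* The Follow up section has data recorded every day of the 5-day intervention. The safety section calls for an assessment at every visit. Only a patient with no evaluation of any kind after dosing is lost, which should be rare.
- *After the 5-day course.* Deaths and withdrawals during the course would be lost. The article foresees deaths before the course is complete, since the Withdrawal or dropout criteria except such patients from the rule on short treatment: "not including the patients who were discharged due to improved health or death due to progression of the illness". Patients who stop early because of discharge or deterioration are largely protected under this reading too. The Precautions section assigns their data to day 6 and continues follow-up to day 28.

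**3. The follow-up sentences**

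One sentence covers all subjects with adverse events. The next gives an endpoint for mild events and SAEs only. On the article's own four-level scale, that leaves moderate and severe non-serious events with follow-up but no stated endpoint.

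**The case against.** The strongest case on the other side is that little is actually lost. SAEs have their own category, so the gravest events are singled out, not hidden. All adverse events must be recorded, patients are seen daily during treatment, and a recorded infusion reaction could reasonably count as a safety evaluation. The safety set wording does not require a scheduled evaluation. The article condenses a fuller protocol, and the form itself, which is not shown, may have a seriousness box. These points stand, and they keep the matter small. They do not remove it, because the article does not merely leave the severity scale and the safety set to a later document. It states both, and as stated they are faulty.

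Several stronger readings are tempting, and the document does not support them:

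- *That the worst events are left out.* SAEs remain countable, and exclusion from the safety set requires that no post-treatment evaluation took place at all.
- *That a severity table by arm could not be interpreted.* No such table is specified. If one were made, its severe row would be incomplete and its SAE row would mix intensities, but it could be read with that caveat.
- *That moderate and severe events go unfollowed.* The preceding sentence covers every subject with an adverse event.
- *That a third to two-thirds of a safety signal could be lost.* With 150 patients per arm, an assumed rate of 1% to 2% gives 1.5 to 3 events, and one omission would be 1/3 = 33% to 1/1.5 = 67% of them. Both the rate and the omission are assumed, so this says nothing about likelihood.
- *That the chi-square test for adverse events, or the lack of an as-treated rule, is a defect.* Handling of small counts and of treatment received commonly belongs to the statistical analysis plan, which the article says will be written.

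**Conclusion.** The point holds as a minor correction. The article places seriousness on the severity scale, so SAEs carry no intensity grade and the severe count omits events that were also serious. This rests on reading the four categories as mutually exclusive, which is their plain sense. The safety set can exclude a treated patient whom the FAS includes. Under the first-dose reading this should be rare. Under the end-of-course reading it could take in deaths and withdrawals during the 5 days. The wording does not settle which reading is meant.

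No rate, bias or loss of signal can be quantified from the document, and no efficacy conclusion is affected. The reason to act is that both definitions concern part of the first primary objective and are cheap to put right.

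**What to change.** 1. Record intensity (mild, moderate, severe) and seriousness (yes or no, against stated criteria) as two separate fields for every adverse event, and report both by arm.
2. Define the safety set as all patients who received any amount of study infusion, with no condition on later evaluation. This also removes the ambiguity of after treatment.
3. Reconcile the sentence on following mild events and SAEs to resolution with the sentence before it, so that the text states what applies to moderate and severe non-serious events.

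The cost is a change of wording in the protocol and analysis plan, plus a small amount of re-coding. If the form holds only one severity field, events already coded as SAEs need an intensity grade assigned, and this should be done before unblinding.

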### Statistical analysis

An independent professional statistician and researcher will develop a complete statistical analysis plan for the trial, prior to the final analysis. The statistical analysis will be performed by the statistician in a blinded manner using the Statistical Analysis System (SAS) software version 9.2. The main analysis will be based on the full analysis set (FAS). According to the intention-to-treat principle, the FAS refers to a set of data on any participants who randomly receive at least one treatment. The per-protocol set (PPS), a subset of the FAS, includes data on only those participants who completed the trial without any violations of or deviations from the protocol. The FAS and PPS will be used for the assessment of efficacy. For the safety assessment, the safety set (SS) will be used, which includes patients who have received at least one safety evaluation after treatment.

All data, including the number of subjects included, drop-outs, elimination conditions, demographics, baseline characteristics, and efficacy and safety assessment, will be analyzed using different approaches. Descriptive and univariate statistics will be used to characterize the study participants and compare the baseline characteristics between the two groups. The primary outcome is the rate of endotracheal intubation, which will be determined by the Cochran-Mantel-Haenszel (CMH) test in the FAS population. We prefer to use the CMH chi-square test because it can deal with confounders of multi-center effects. Two-sided tests will be performed for all the other statistical analyses. The CMH chi-squared test or Fisher’s exact test will be used for comparing the categorical outcomes. The continuous outcomes will be analyzed by Student’s *t* test, while the AEs will be presented using descriptive statistics and compared using a chi-square test. A *P* value <0.05 will be considered to indicate statistical significance. Missing data will be explored and adjusted using the imputation method.

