### Blinding

The blinding method is consistent with our previous study [28]. Briefly, both investigators and subjects will be blinded, while drug administrators and dispensing nurses are aware of the group allocation. But the drug administrators and dispensing nurses will not be involved in data collection and analysis. In order to mask the investigators, drug administrators and the investigators would have independent authority to log into the central randomization system. The subjects’ group allocation is concealed by the randomization system, and both the paper and electronic case report form (CRF) collect only the patient’s random number, which does not indicate the group allocation. The evaluators and statistician will also be masked until completion of the visit and analysis. Both XBJ and placebo are administered using a photophobic infusion set to avoid the subjects being aware of the group information.

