### Intervention

#### Trial treatment methods

After randomization, the participants will be categorized into two groups receiving either XBJ injection (specification, 10 mL/piece; packaging, 10 pieces/container) or placebo (0.9% NaCl injection, suggested specification, 200 mL). XBJ injection is provided and manufactured by Tianjin Chase Sun Pharmaceutical Co., Ltd., Tianjin, China (lot number Z20040033). The 0.9% NaCl injection is provided by each sub-center. Both groups will receive routine medication according to the GOLD 2016 guideline [17].

The treatment group will receive routine medication plus XBJ injection every 12 h (q12h) for 60 min; a total of 50 mL XBJ will be diluted to 150 mL using 100 mL of 0.9% NaCl injection. The control (placebo) group will receive routine medication plus 0.9% NaCl injection (dosage 150 mL, q12h for 60 min). The dosage and speed of injection for the placebo and XBJ injection groups (150 mL, q12h, intravenous drip for 60 min) will be identical. The patients will receive the research medication within 24 h of enrollment, and the treatment period is 5 days.

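### The primary analysis set is called intention-to-treat but leaves out randomised patients who never received a dose, so an intubation between randomisation and the first infusion is not counted

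*Protocol article*

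**What the plan says.** The Statistical analysis section bases the main analysis on the full analysis set (FAS) and, invoking intention to treat, defines it in one sentence: "the FAS refers to a set of data on any participants who randomly receive at least one treatment". The wording is awkward, but the natural reading is randomised and treated at least once. The primary outcome is the endotracheal intubation rate, "which will be determined by the Cochran-Mantel-Haenszel (CMH) test in the FAS population". No analysis of all randomised patients is stated.

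Four other sections bear on who falls outside that set:

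- Withdrawal or dropout criteria: patients who did not get the research medication are among those not included in the analysis. The section does not say which analysis set this refers to.
- Trial treatment methods: "The patients will receive the research medication within 24 h of enrollment".
- Exclusion criteria: patients already on invasive mechanical ventilation cannot enter.
- Randomization and Blinding: after the random number exists, drug administrators pass the medication to the nurses according to the group. Under the blinding arrangement, "both investigators and subjects will be blinded, while drug administrators and dispensing nurses are aware of the group allocation". These unblinded staff take no part in data collection or analysis.

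**The concern.** The label and the definition disagree. An intention-to-treat set holds everyone randomised, whereas this one holds everyone randomised and dosed. The difference concerns the endpoint directly. Nobody is on invasive ventilation at entry, so an intubation after randomisation and before the first infusion is a new primary event, and the stated rule removes it. The same rule removes a pre-dose death, which is a secondary outcome, and a pre-dose withdrawal.

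Leaving out never-dosed patients is commonly accepted when knowledge of the arm cannot influence whether treatment starts. This protocol does not secure that condition, because the people who release and dispense the first infusion know the arm. The population is acutely ill, so deterioration, which is what the primary outcome measures, may also be the reason a first dose is missed. If missed first doses differed by arm for any reason, membership of the primary set would depend on allocation and the observed difference could shift without any treatment effect.

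**Working it through.** **Inputs (Sample size section).** Intubation rates 15.2% (control) and 4.7% (XBJ); two-sided α = 0.05; β = 0.2; 127 per group before attrition; 15% attrition; 150 per group.

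**1. Reproducing the plan's figure.** With pooled variance under the null and no continuity correction,

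n = [1.960·√(2·p̄·(1−p̄)) + 0.842·√(p1(1−p1) + p2(1−p2))]² / (p1−p2)²

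Here p̄ = (0.152 + 0.047)/2 = 0.0995 and p1−p2 = 0.105. The result rounds up to 127, as stated. Then 127/0.85 = 149.4, so 150 per group, also as stated.

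**2. Expected events.** Control 150 × 0.152 = 22.8, about 23. XBJ 150 × 0.047 = 7.05, about 7.

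**3. Weight of one dropped XBJ intubation.** 1/150 = 0.67 percentage points, and 0.67/4.7 = 14% of the planned rate. Taking the patient out of the denominator too changes little: 7/150 = 4.67% becomes 6/149 = 4.03%, a fall of 0.64 points.

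**4. When that changes the conclusion.** These are illustrative outcomes, with events dropped from the XBJ arm only and an uncorrected chi-square test without centre strata:

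| Control | XBJ, all randomised | p | XBJ after dropping | p |
|---|---|---|---|---|
| 23/150 | 13/150 | 0.076 | 12/149 (one) | 0.0503 |
| 23/150 | 13/150 | 0.076 | 11/148 (two) | 0.032 |
| 23/150 | 14/150 | 0.114 | 11/147 (three) | 0.034 |
| 23/150 | 23/150 | 1.00 | 11/138 (twelve) | 0.053 |

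In the near-threshold examples, two or three one-sided exclusions cross 0.05 and one does not. With equal arms, even twelve do not.

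**5. Power if all randomised patients are analysed.** At the design rates, 150 per group give 86.3%. Suppose m patients per group are intubated before dosing (m is an assumption) and the design rates hold in the rest. The rates become [(150−m)·p + m]/150. For m = 3 these are 16.9% and 6.6%. Power is then:

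- m = 1: 84.0%
- m = 2: 81.7%
- m = 3: 79.3%
- m = 5: 74.7%

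In the dosed-only set it stays at 85–86% over the same range.

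**The case against.** **The strongest reply is that no mechanism for bias is stated.** A reader might infer from the Blinding section that unblinded staff decide who enters the primary analysis, and that randomisation therefore no longer protects the comparison. The protocol does not support that. It gives drug administrators a procedural step, passing on the medication after randomisation, and assigns neither them nor the nurses any discretion to start, delay or withhold it. Investigators and patients are blinded. If missed first doses are unrelated to arm, the two dosed groups remain comparable. This stands: the bias is possible, not demonstrated. But keeping these staff out of data collection and analysis does not by itself make a missed first dose independent of arm.

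**The 24 h is an outer limit and runs from enrolment.** The gap that matters runs from randomisation to the first infusion. Its length is not given and may be shorter. The entry criteria also exclude shock and an oxygenation index below 150, which removes many patients likely to need early intubation. Both points stand, and both suggest small numbers.

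**The size cannot be derived.** One might assume that 1–3% are never dosed, 1.5–4.5 patients per arm, and set that against the 7 expected XBJ events. That treats every undosed patient as intubated. At the plan's own rates, such patients would carry only 0.07–0.21 events in XBJ (1.5 × 0.047 to 4.5 × 0.047) and 0.23–0.68 in control (1.5 × 0.152 to 4.5 × 0.152). Patients who deteriorate early would carry more, but the protocol gives no figure. The p-value examples above also start from chosen borderline results and drop events from one arm only.

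**A later analysis plan might settle it.** The protocol foresees one, but it already fixes the definition and the label itself, so this is not a detail left open.

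**Conclusion.** The point holds as a mismatch between label and definition with a direct consequence. The set used for the primary test is described as intention-to-treat, yet it leaves out randomised patients who were never dosed, including any intubated before the first infusion. The Withdrawal or dropout criteria reinforce the omission.

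Arm-related selection is a risk that the protocol leaves open, not one that it shows. The number of patients affected is unknown and probably small. Each XBJ intubation dropped is worth about 0.67 points, or 14% of that arm's planned rate. A few dropped from one arm could decide a result already close to the threshold, but would not create significance from equal arms. The conclusion rests on reading the definition as randomised and treated at least once, which the Withdrawal or dropout criteria support.

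**What to change.** - **Statistical analysis:** define the primary analysis set as all randomised patients in their assigned arm. Count every intubation from randomisation to day 28, whether or not a dose was given. Counting from randomisation also gives undosed patients a start point, since the Abstract and the Follow up section count from treatment.
- **Sensitivity analysis:** keep the at-least-one-dose set for this purpose.
- **Withdrawal or dropout criteria:** state that the never-dosed exclusion applies to the per-protocol set only. If only the Statistical analysis section is changed, the protocol will contradict itself on exactly these patients.

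The cost is two short text changes and day-28 follow-up of the few undosed patients, for which the telephone or message contact already planned after discharge can serve. Untreated patients dilute the contrast slightly. At the design rates the planned 150 per group give 86.3% power, so the change in itself needs no larger sample. Power would fall just below 80% only if about three patients per group were intubated before dosing, under the assumptions shown in the working.

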#### Exclusion criteria

Patients meeting any of the following criteria will be excluded from the trial.Pregnant and lactating women.Allergic to XBJ and its ingredients, or have severe allergies.Exacerbation observed for > 72 h.Mental illness with poor compliance.Severe primary disease (active pulmonary tuberculosis, asthma, cystic pulmonary fibrosis, pulmonary sarcoidosis, pulmonary interstitial fibrosis, unresectable tumors, blood diseases, Alzheimer’s disease, or HIV).Accompanied by pulmonary embolism, shock, diffuse intravascular coagulation (DIC), acute myocardial infarction, upper gastrointestinal bleeding, pneumothorax, cardiac function grade ≥ IV, severe liver and kidney dysfunction (sequential organ failure assessment (SOFA) score liver or kidney single ≥ 3 points).Combined with severe hypoxemia, patients with oxygenation index < 150 or invasive mechanical ventilation.Participation in other clinical trials in the previous 30 days.Patients who are unsuitable for participation or unable to participate in this trial according to the judgment of the investigators (hemodialysis for > 1 month after organ transplantation, existing risk of potential medical disputes, and heart failure limiting the amount of liquid intake).

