### Sample size

A previous study [27] by the Collaborative Research Group of Noninvasive Mechanical Ventilation for COPD showed that the tracheal intubation rate in the routine treatment group (171 cases) was 15.2%, while it was 4.7% in the group receiving early noninvasive positive pressure ventilation plus routine treatment (171 cases). According to the literature, presuming that the rate of tracheal intubation in the XBJ group was reduced from 15.2% to 4.7%, the sample size was calculated according to the parameters α = 0.05 (two-sided test) and β = 0.2. Comparing the rates of the two groups with respect to the sample size estimation formula, we calculated that 127 patients should be recruited in each group. Considering an attrition rate of < 15%, the eligible participants in each group should be > 149. Therefore, we determined that the sample size should be 150 in each group (*n* = 300 in total).

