#### Secondary outcome measures

The secondary outcome measures will be:Changes in immune indicators (detected by flow cytometry).Changes in inflammation indicators (detected by enzyme-linked immunosorbent assay).Respiratory support: the duration of oxygen therapy, high-flow humidification oxygen therapy, noninvasive mechanical ventilation, and invasive mechanical ventilation.Mortality rate after 28 days.Blood gas analysis (including blood lactate).Improvement in acute physiology and chronic health evaluation II (APACHE II) scores; the evaluation of improvement is based on differences in the APACHE II scores before and after the intervention.Improvement in clinical symptoms based on improvement in dyspnea, cough, sputum, and the use of accessory respiratory muscles (using the scoring system shown in Table 2). According to the differences in the scores before and after the intervention, the evaluation criteria are as follows:Significantly effective: the score decreased ≥ 3;Effective: the score decreased from 1 to 3;Ineffective: no change in the score;Exacerbation: the score increased ≥ 1;Name, dosage, and duration of antibiotic use.Name, dosage, and duration of corticosteroid use.Changes in laboratory inspection indicators.Incidence of complications.Length and cost of intensive care unit (ICU) stay.Length and cost of hospitalization.

**Table 2 Tab2:** The clinical symptoms scoring system of AECOPD

Score	Dyspnea	Cough	Sputum production	Use of accessory respiratory muscles
0	–	No cough	No sputum	No neck muscle tension and periodic contraction
1	Shortness of breath when flat on the ground or walking up one floor level	Intermittent cough, but no symptoms at night	Sputum volume ≤ 30 mL the whole day and night	Neck muscle tension, but no obvious muscle activity
2	Shortness of breath when walking with peers	Sometimes cough, which probably affects sleep	Sputum volume ≥ 30 mL and ≤ 50 mL	Visible slight contraction of the neck muscles
3	Need to stop so as to breathe when walking at their own speed	Frequent cough affecting sleep	Sputum volume ≥ 50 mL and ≤ 100 mL	Moderate contraction of the neck muscles, not with clavicular fossa and intercostal retraction
4	Shortness of breath when dressing or undressing	–	Sputum volume ≥ 100 mL	Strong contraction of the neck muscles, with abdominal contradictory movement

The evaluation criteria for the improvement in clinical symptoms is according to the total scores of the 4 items

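### The primary intubation test adjusts for centre only; adding a baseline severity value would gain a modest amount of power at little cost

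*Protocol article*

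**What the plan says.** Under Statistical analysis, the protocol article states: "The primary outcome is the rate of endotracheal intubation, which will be determined by the Cochran-Mantel-Haenszel (CMH) test in the FAS population". It prefers this test because "it can deal with confounders of multi-center effects". Centre is the only factor named. Baseline characteristics are to be described and compared between arms, but none is carried into the primary comparison. The Randomization section names no stratification by severity. A full statistical analysis plan is to be written before the final analysis and is not at hand.

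Three other places bear on the point:

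- Primary outcome measures says that intubation is probably a marker of how severe the exacerbation is.
- Secondary outcome measures includes APACHE II, where "the evaluation of improvement is based on differences in the APACHE II scores before and after the intervention". A pre-intervention score is therefore part of the plan.
- Exclusion criteria rules out "patients with oxygenation index < 150 or invasive mechanical ventilation". The oxygenation index has to be looked at before a patient can be entered.

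**The concern.** Patients enter with a wide spread of illness. The admission indications in the inclusion criteria run from lack of support at home to unstable haemodynamics. If baseline severity predicts intubation, a test that ignores it treats predictable variation between patients as noise. The comparison rests on few events, so some loss of precision is worth avoiding when the remedy needs no extra patients.

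The loss matters more if the true effect is smaller than planned, which is a realistic prospect. The Sample size section takes both rates from a trial of early noninvasive ventilation, not from data on XBJ. Both arms here receive ventilatory support as part of routine care.

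**Working it through.** **Inputs from the Sample size section.** "presuming that the rate of tracheal intubation in the XBJ group was reduced from 15.2% to 4.7" per cent; "α = 0.05 (two-sided test) and β = 0.2"; "we calculated that 127 patients should be recruited in each group"; "Considering an attrition rate of < 15" per cent; 150 per arm enrolled.

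**The plan's own figure.** Two proportions, pooled variance under the null, no continuity correction, with mean rate (0.152 + 0.047)/2 = 0.0995:

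n = [1.960·√(2 × 0.0995 × 0.9005) + 0.8416·√(0.152 × 0.848 + 0.047 × 0.953)]² / 0.105²
= (0.8297 + 0.3508)² / 0.011025 = 126.4, rounded up to 127.

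127/0.85 = 149.4, rounded up to 150. Both stated figures reproduce. The same formula gives power of 80.2% at 127 per arm and 86.3% at 150 per arm.

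**Expected events.** At 150 per arm: 150 × 0.152 + 150 × 0.047 = 22.8 + 7.05 = 29.85, or about 3.3 in each of nine centres. At 127 per arm: 127 × 0.199 = 25.3.

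**Assumptions.** The documents give neither the predictive strength of baseline severity nor the spread between centres. Both are assumed.

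**Test A: CMH on residuals.** Fit a logistic model of intubation on the baseline covariates, without treatment arm. Then apply the centre-stratified CMH mean-score test to its residuals. Settings: 150 per arm, nine unequal centres, centre SD 0.4 on the logit scale, 3,000 simulated trials per setting.

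| Rates | Assumed AUC | CMH by centre | Adjusted |
|---|---|---|---|
| 15.2% vs 4.7% | 0.71 / 0.77 / 0.81 | about 87% | 88 / 90 / 91% |
| 15.2% vs 4.7% | 0.71 / 0.75 / 0.83 | 87–88% | 89 / 89 / 92% |
| 15.2% vs 7.6% | 0.71 / 0.77 / 0.81 | 54–55% | 57 / 59 / 62% |
| 15.2% vs 7.6% | 0.71 / 0.75 / 0.83 | 55–56% | 57 / 60 / 63% |

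Type I error of the adjusted test was 4.6–5.1% in the first set and 4.7–5.3% in the second. A further run of 2,000 trials per setting, over three rising strengths of severity, gave:

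- 87–89% against 88 / 91 / 92% at the planned rates;
- 53–55% against 56 / 58 / 63% at 15.2% vs 7.6%;
- type I error of 4.9–5.1%.

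The simulation error of one power figure is about √(0.87 × 0.13/3000) = 0.6 points at the planned rates and √(0.55 × 0.45/3000) = 0.9 points at the smaller effect. The gain is therefore roughly 1 to 5 points at the planned rates and roughly 3 to 8 points at 15.2% vs 7.6%. At the weakest strength, one run was nearer 1 to 2 points for the smaller effect.

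**Test B: logistic likelihood-ratio test with centre terms and one severity score.** Settings: nine centres of equal expected size, centre SD 0.3, AUC about 0.66 / 0.71 / 0.75 / 0.83 (severity and centre together).

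- 150 per arm: CMH 86–88%; adjusted 89.1 / 89.3 / 89.8 / 92.1%.
- 127 per arm: CMH 80–82%; adjusted 84.0 / 83.1 / 85.6 / 88.5%.
- Type I error: CMH 4.3–5.7%; adjusted 5.2–6.3%.

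The gains are of the same order, about 1 to 6 points at 150 per arm. Carrying nine centres as model terms on 25 to 30 events pushes the type I error slightly above 5%.

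**Size of the smaller effect.** 15.2% vs 7.6% is a difference of 7.6 points, and 7.6/10.5 = 72% of the planned risk difference. On the log odds scale it is 0.779/1.290 = 60%. Half the planned difference would be 15.2% vs 9.95%, where unadjusted power is only about 28% by the formula above.

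**The case against.** The strongest reply is that nothing is wrong. A centre-stratified CMH test is valid for a randomised binary outcome, it holds its type I error, and at 150 per arm it exceeds the 80% target. Covariates are often left to the statistical analysis plan, and the article does not rule out an adjusted analysis. The gain is small, and it depends on a predictive strength that no document gives. Excluding the most hypoxaemic and the already ventilated patients may lower that strength.

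Most of this stands, and it sets the weight of the point. It does not remove the point, because the article names the primary test and gives its reason. The choice is stated, not left open.

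Four stronger readings are tempting but not supported:

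- A reader might infer that chance imbalance in severity biases the planned test. It does not. Such imbalance runs in either direction and is already covered by the test's type I error. What is lost is precision.
- A reader might infer that intubation risk varies far more by severity than by centre. The documents quantify neither.
- A reader might infer that both severity values are known before randomisation for every patient. The article says only that APACHE II is scored before and after the intervention. The items it lists for entry at randomisation include neither value, and the assessment schedule is in a figure not reproduced here. Completeness of the baseline values is likely but not shown.
- A reader might take 15.2% vs 7.6% as half the planned effect. It halves the rate, not the risk difference.

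**Conclusion.** The planned primary test is sound and adequately powered on the design assumptions, but less efficient than it could be at almost no cost. The size of the loss rests on the assumed AUC of 0.71 to 0.83, all 150 per arm being analysed, and the assumed centre spread; a weaker predictor would bring less. For scale, moving from 127 to 150 per arm raises power by 86.3 − 80.2 = 6.1 points, so at the planned effect the gain is at most somewhat less than that. This is a worthwhile improvement, not a correction that the trial's validity depends on.

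**What to change.** Before unblinding, specify in the statistical analysis plan a primary test that keeps the centre strata and adjusts for one or two baseline severity values: APACHE II, and the oxygenation index if it is recorded. With about 30 events, no more than two.

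- **Test.** For example, one logistic model of intubation on these values, fitted without treatment arm, then the centre-stratified CMH mean-score test on its residuals. This avoids the slight type I inflation seen when centres enter as model terms.
- **Estimate.** A standardised risk difference with 95% confidence interval from the same covariates. State in advance that the test decides significance, since test and interval can differ at the margin.
- **Missing baseline values.** One simple prespecified imputation that does not use treatment arm, so that no patient leaves the full analysis set.
- **Sensitivity.** The unadjusted centre-stratified CMH test as now described.

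The cost is a few lines of code and the need to fix the covariates in advance. No new visits or patients are required. Because the protocol names the primary test, the change may also need the addendum and ethics re-review that the Ethics section requires for protocol changes.
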